16.6.2 Secondary Analyses

16.6.2.1 Response Rate: All patients who were registered to the study and started treatment will be included in the response rate analysis. Response rate will be defined as the proportion of patients displaying response (PR or CR) at 3 months post treatment; patients who did not have a 3-month post treatment assessment will be considered a non-response. A chi-square test will be used to compare response rates between the two treatment arms. Absolute risk difference and relative risk will be calculated; 95% confidence intervals will be calculated using the score method.

16.6.2.2 Local control: All patients who were registered to the study and started treatment will be included in the local control analysis. A local recurrence event is any event defined as disease relapse occurring in the area treated before with radiation (anything included within the 95% isodose line). The local control interval will be defined as the number of days from end of radiation treatment until first local recurrence within 24 months post radiation treatment; censoring will occur at date of patient death or date of last disease evaluation (based on imaging and clinical exam). Local control rates will be estimated separately for the two treatment groups at 3-, 6-, 12-, 18, and 24-months post radiation treatment using the Kaplan-Meier method. Hazard ratio and 95% confidence interval for comparison of local recurrence between the two treatment arms will be estimated from a Cox proportional hazards model.

16.6.2.4 Quality of life: FACIT-Fatigue scores along with validated subscales given as SOC for Lymphoma patients will be collected from baseline to up to 3 months after radiation treatment. The FACIT Fatigue consists of 13 Likert-scale items scored 0 (not at all) to 4 (very much). We will calculate the fatigue subscale score at each assessment by first reverse scoring the following items: HI7, HI12, An1, An2, An3, An4, An8, An12, An14, An15, An16 by subtracting the response from 4 and then sum the 13 items to obtain a score. Then multiple the sum of the items by the number of items in the subscale (13), then divide by the number of items the patient answered. The Fatigue Subscale score ranges from 0 to 52 where a higher score indicates a better quality of life. We will estimate the difference between treatment arms in the trajectory (slope) of the Fatigue Subscale score including all available scores from end of treatment to 3 months post RT in a longitudinal mixed effects regression model with a random effect for patient. Fixed effects will include an indicator variable for treatment arm (1=9 Gy, 0=24 Gy), time defined as the number of weeks (7 days) from end of treatment to FACIT-Fatigue assessment (continuous), and an interaction term for treatment arm and time. The estimates from the interaction term along with 95% confidence interval (profile likelihood) will be interpreted as the difference in trajectories between treatment arms. A likelihood ratio test will be used to compare treatment arms on the difference in trajectories of fatigue subscale score.

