Event monitoring is the period when the participant is no longer following the protocol test schedule due to disease progression and/or the patient was started on a new non-study anti-cancer treatment. During Event Monitoring, the data collection schedule is dictated by the protocol, but the visit schedule is determined by clinical practice at each participating site. During the Event Monitoring Phase of the study, the participant is being monitored for key study events such as new non-study anti-cancer treatments given, new primaries, and death. Samples from biospecimens collected in the course of clinical care may be requested but cannot be required of the participant.

##

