## **13.0 Treatment/Follow-up Decision at Evaluation of Patient**

13.1 Those patients who will not receive any radiation treatment or who will receive radiation treatment elsewhere will go off study per **Section 13.7**.

13.2 Patient who are CR, PR, or SD will continue to obtain PET or CT scans at each clinically indicated follow up for up to 24 months after the completion of radiation treatment.

13.3 Patients who develop PD or withdraw from further follow up assessments will be followed for event monitoring only per **Section 4.0**.

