### 16.5 Statistical Design

16.5.1 Decision Rules

16.5.1.1 A two group χ^2^ test of equal proportions in acute adverse events will be conducted to determine the efficacy in acute toxicity reduction within the treatment arm. If the p-value of the statistical test is less than 0.10 then the treatments will be considered significantly different in the direction of the point estimates. Therefore, a significant difference in the direction of the experimental arm will deem the treatment favorable and worth consideration in future trials. If the test is non-significant then the experimental arm will not be considered significantly different in toxicity profile and therefore, not considered for future trials. It is also important to consider the local control rate when deciding whether to pursue further study. In the FoRT trial, the 2-year local progression-free rate was 94.1% after 24 Gy and 79.8% after 4 Gy. If the observed 2-year probability of local control is more than 7% inferior with 9 Gy versus 24 Gy, then we will not consider future trials. For example, if the 2-year local control rate is 94.1% after 24 Gy, and less than 87.1% after 9 Gy then we would not pursue further study.

16.5.1.2 Over Accrual: We will accrue approximately 10% over-accrual (112 total patients, 56 per arm) in order to ensure 102 evaluable patients as described in previous sections. The first 102 evaluable patients will be utilized for analysis of the primary endpoint.

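### Local control: patients who die are censored at death, not at their last disease evaluation, so unexamined time can slightly inflate the 2-year estimate behind the 7-point rule

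*Protocol*

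**What the plan says.** Section 16.6.2.2 defines the local control interval as the "number of days from end of radiation treatment until first local recurrence within 24 months post radiation treatment", and states that "censoring will occur at date of patient death or date of last disease evaluation (based on imaging and clinical exam". Nothing orders the two dates. Rates are then estimated by arm up to "24-months post radiation treatment using the Kaplan-Meier method".

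The 24-month figure is used in a decision. Section 16.5.1.1 sets the condition: "observed 2-year probability of local control is more than 7% inferior with 9 Gy versus 24 Gy, then we will not consider future trials". The illustration given there is "if the 2-year local control rate is 94.1% after 24 Gy, and less than 87.1% after 9 Gy".

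Four other places govern how long the treated site is examined:

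- Section 7.2.2 sets imaging at 3, 6, 12, 18 and 24 months. Footnote 1 of the section 4.0 table leaves follow-up assessments to the clinician.
- Section 13.3: "Patients who develop PD or withdraw from further follow up assessments will be followed for event monitoring only".
- Section 4.0, on that phase: "During the Event Monitoring Phase of the study, the participant is being monitored for key study events such as new non-study anti-cancer treatments given". The list also names death and new primaries, but not local status.
- Section 11.4 instead has scans running on until in-field progression, death or month 24.

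**The concern.** Two patients whose treated site was last examined on the same day carry the same information about local control. Under section 16.6.2.2 the one who lives leaves the risk set on that day, while the one who later dies stays in it until death. If scheduled visits pass in between, the second patient enlarges the denominator at those visits although the site was not under scheduled evaluation.

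This inflates the local control estimate, and more so in the arm with more recurrences. If that is the reduced-dose arm, the gap read by the 7-point rule tends to look smaller than it is. The rule acts on the observed estimate, without an interval, so even small shifts count near the threshold.

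**Working it through.** **Plan's own figure.** 94.1 − 7 = 87.1, as in section 16.5.1.1.

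**Reading the rule.** A last evaluation is never later than death. If the earlier date applied, the death date would never be used. Both dates have a use only under rule A: deaths censored at death, others at last evaluation. Rule B censors everyone without recurrence at last evaluation.

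**Mechanism.** S(24) = ∏(1 − dⱼ/nⱼ) over visits with recurrences. A patient last evaluated at *a* who dies at *b* counts in nⱼ for visits between *a* and *b* under A but not under B. With the dⱼ unchanged, A can never give a lower estimate than B. The two agree if no visit with a recurrence falls between *a* and *b*.

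**Spacing alone.** Take 56 patients (accrual per arm, section 16.5.1.2), with 1, 2, 2 and 2 recurrences found at months 6, 12, 18 and 24. Six patients last evaluated at month 18 die at month 22. Both rules give 51/56 × 43/45 = 87.02%, so there is no bias.

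**Visits passed unexamined.** Same arm, but the patients who die at month 22 were last evaluated at month 6:

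| Deaths | Rule A | Rule B |
|---|---|---|
| 6 | 51/56 × 43/45 = 87.0% | 55/56 × 43/49 = 86.2% |
| 8 | 51/56 × 41/43 = 86.8% | 55/56 × 41/47 = 85.7% |

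**Bounding case for the 7-point rule.** Take 51 per arm (section 16.1), 3 recurrences on 24 Gy and 6 on 9 Gy. Suppose *k* late deaths occur on 9 Gy only, each last evaluated before any recurrence was found.

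- Rule A: 48/51 − 45/51 = 94.12 − 88.24 = 5.88 points.
- Rule B, k = 4: 94.12 − 41/47 (87.23) = 6.88 points.
- Rule B, k = 5: 94.12 − 40/46 (86.96) = 7.16 points, which crosses the threshold.

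**Expected size.** The protocol gives no death or progression rates for this population, so those below are assumptions. The simulation used exponential times, true 24-month local control of 94.1% and 87.1%, and visits at 3, 6, 12, 18 and 24 months. Evaluation stopped at the visit that finds distant progression. Bias was estimated from 30,000 patients per arm, and the change of decision from 2,000 trials of 51 per arm. Survival columns are 24-month survival without, and counted from, progression.

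| Distant PD | Survival before PD | Survival after PD | Missed visits | Deaths by month 24 | A − B, 24 Gy | A − B, 9 Gy | Change in gap | Decision changes |
|---|---|---|---|---|---|---|---|---|
| 30% | 97% | 90% | 0% | 4.1% | 0.02 | 0.04 | 0.02 | 0.25% |
| 30% | 97% | 70% | 0% | 7.3% | 0.05 | 0.10 | 0.05 | 0.65% |
| 30% | 97% | 70% | 20% | 7.4% | 0.05 | 0.12 | 0.07 | 0.55% |
| 30% | 95% | 50% | 20% | 13.1% | 0.10 | 0.18 | 0.08 | 0.45% |
| 50% | 90% | 50% | 20% | 21.9% | 0.17 | 0.42 | 0.25 | 1.95% |

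Other runs, with death independent of progression, changed the gap by 0.01 to 0.02 points at 5% deaths and by 0.06 to 0.12 at 29%. With no distant progression and every visit done, the difference was zero at every death rate.

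**Yardstick.** The standard error of the gap, ignoring censoring, is √[(0.871 × 0.129 + 0.941 × 0.059)/51] = 5.7 points.

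**The case against.** **Wording.** The two dates are joined by a bare conjunction, and exact censoring dates are often settled in an analysis plan, which is not at hand. This stands in part: the reading is an inference. But the protocol states the rule itself, and only this reading gives the death date a function. Censoring deaths is usual for local control; the point concerns only the date.

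**Follow-up.** Section 11.4 has scans continuing to death, and if that is what happens the bias largely goes. Section 13.3 says otherwise for patients with progression, so section 11.4 cannot be relied on while the two conflict.

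**Stronger readings.** A reader might infer that six-monthly scanning itself pads the risk set. It does not, as the 87.02% result shows. A reader might also infer that patients in event monitoring cannot have a local event recorded. The documents do not say so: the list in section 4.0 is open-ended, visits follow clinical practice, and section 16.6.2.2 counts any relapse in the treated area. What lapses is scheduled evaluation.

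**Size.** Both arms shift the same way, and the net change in the gap is far below its standard error. This stands. The worked examples are stress cases. The early-stage 10-year survival of 60% to 70% in section 1.0 implies, at a constant hazard, 1 − 0.70^0.2 = 7% to 1 − 0.60^0.2 = 10% deaths by 24 months, or about 4 to 5 of 51 per arm. Sections 3.1.3 to 3.1.5 admit any stage, relapsed or refractory disease and performance status up to 3, so mortality may be higher, but nothing in the protocol supports 29%.

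**Conclusion.** The point holds as a small defect in the choice of censoring date. It needs patients who stop evaluations, pass at least one scheduled visit and then die within 24 months.

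Under assumed deaths of about 5% to 29%, local control is overstated by about 0.02 to 0.4 points in one arm. The arm gap changes by about 0.01 to 0.2 points, with 0.25 in the harshest run. The decision changed in about 0.3% to 2% of simulated trials, with the true gap placed at 7 points, where the rule is most sensitive.

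The error within an arm is never downward. It narrows the gap on average, provided the reduced-dose arm has more recurrences and unexamined deaths are spread similarly; a single trial can go the other way. A reader might infer that the 7-point rule is seriously compromised. The figures do not support that: the threshold is crossed only in stress cases, such as five late unexamined deaths confined to one arm. This is a cheap improvement of low priority.

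**What to change.** Change one sentence in section 16.6.2.2: censor every patient without local recurrence, including those who die, at the last disease evaluation that documented no recurrence at the treated site. The cost is a slightly smaller risk set and slightly wider intervals.

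Reconcile sections 11.4 and 13.3 on whether disease evaluations continue after progression outside the field, since the size of the bias depends on it.

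A 2-year estimate with death as a competing event is an optional check.

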**Fatigue – Short Form 13a (FACIT-Fatigue)**

**Please respond to each question or statement by marking one box per row.**

|  | **During the past 7 days…** | **Not at all** | **A little bit** | **Somewhat** | **Quite a bit** | **Very much** |
| --- | --- | --- | --- | --- | --- | --- |
| HI7 | I feel fatigued | 🞎  1 | 🞎  2 | 🞎  3 | 🞎  4 | 🞎  5 |
|  |  |  |  |  |  |  |
| HI12 | I feel weak all over | 🞎  1 | 🞎  2 | 🞎  3 | 🞎  4 | 🞎  5 |
|  |  |  |  |  |  |  |
| AN1 | I feel listless ("washed out") | 🞎  1 | 🞎  2 | 🞎  3 | 🞎  4 | 🞎  5 |
|  |  |  |  |  |  |  |
| AN2 | I feel tired | 🞎  1 | 🞎  2 | 🞎  3 | 🞎  4 | 🞎  5 |
|  |  |  |  |  |  |  |
| AN3 | I have trouble starting things because I am tired | 🞎  1 | 🞎  2 | 🞎  3 | 🞎  4 | 🞎  5 |
|  |  |  |  |  |  |  |
| AN4 | I have trouble finishing things because I am tired | 🞎  1 | 🞎  2 | 🞎  3 | 🞎  4 | 🞎  5 |
|  |  |  |  |  |  |  |
| AN5 | I have energy | 🞎  5 | 🞎  4 | 🞎  3 | 🞎  2 | 🞎  1 |
|  |  |  |  |  |  |  |
| AN7 | I am able to do my usual activities | 🞎  5 | 🞎  4 | 🞎  3 | 🞎  2 | 🞎  1 |
|  |  |  |  |  |  |  |
| AN8 | I need to sleep during the day | 🞎  1 | 🞎  2 | 🞎  3 | 🞎  4 | 🞎  5 |
|  |  |  |  |  |  |  |
| AN12 | I am too tired to eat | 🞎  1 | 🞎  2 | 🞎  3 | 🞎  4 | 🞎  5 |
|  |  |  |  |  |  |  |
| AN14 | I need help doing my usual activities | 🞎  1 | 🞎  2 | 🞎  3 | 🞎  4 | 🞎  5 |
|  |  |  |  |  |  |  |
| AN15 | I am frustrated by being too tired to do the things I want to do | 🞎  1 | 🞎  2 | 🞎  3 | 🞎  4 | 🞎  5 |
|  |  |  |  |  |  |  |
| AN16 | I have to limit my social activity because I am tired | 🞎  1 | 🞎  2 | 🞎  3 | 🞎  4 | 🞎  5 |

English (Universal)

Copyright 1987, 1997 by [name].

© 2008-2023 PROMIS Health Organization (PHO)

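### The FACIT-Fatigue scoring rule in Section 16.6.2.4 assumes items coded 0–4, but the Appendix II form prints 1–5 with AN5 and AN7 already reversed, and no recoding step links the two

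*Protocol*

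**What the plan says.** Protocol Section 16.6.2.4 (Quality of life) sets out the scoring in full. It describes the instrument as "13 Likert-scale items scored 0 (not at all) to 4 (very much"). It lists the items to reverse: "HI7, HI12, An1, An2, An3, An4, An8, An12, An14, An15, An16". That is 11 items; An5 and An7 are not among them. The 11 are reversed "by subtracting the response from 4 and then sum the 13 items to obtain a score", so An5 and An7 enter as recorded. The sum is multiplied by 13 and divided by the number of items answered. The result is described thus: "The Fatigue Subscale score ranges from 0 to 52 where a higher score indicates a better quality of life". The analysis is a mixed model for the slope of this score from end of treatment to 3 months, with the arm-by-time interaction as the treatment comparison.

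The Test Schedule (Section 4.0) names the Appendix II form as the one collected. On that form the fatigue-worded items carry ascending codes, for example "HI7 | I feel fatigued | 🞎 1 | 🞎 2 | 🞎 3 | 🞎 4 | 🞎 5". The two positively worded items carry descending codes: "AN5 | I have energy | 🞎 5 | 🞎 4 | 🞎 3 | 🞎 2 | 🞎 1" and "AN7 | I am able to do my usual activities | 🞎 5 | 🞎 4 | 🞎 3 | 🞎 2 | 🞎 1". The columns run from *not at all* on the left to *very much* on the right in every row.

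**The concern.** The rule and the form use different codings, and the protocol does not say how to get from one to the other. The difference has two parts. First, the printed codes start at 1, not 0, so 4 minus a response of 5 gives −1. Second, the form has already turned AN5 and AN7 round, so that 5 means no energy or no usual activity. A rule that adds these two items unchanged expects a high value to be good. Applied to the printed codes, it rewards a patient for having no energy.

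FACIT-Fatigue is the only patient-reported measure among the secondary goals (the COST questionnaire is exploratory). A scoring error here would enter the interaction estimate that is to be reported as the difference between arms.

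**Working it through.** **Inputs.** From Section 16.6.2.4: values 0–4, 11 items reversed as 4 minus response, AN5 and AN7 added as recorded, stated range 0 to 52. From the Appendix II form: the 11 items printed 1 to 5; AN5 and AN7 printed 5 to 1. All 13 items are taken as answered, so the proration factor is 13/13 = 1.

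**Step 1: reproduce the stated range on the stated coding.** Score = sum of (4 − response) over 11 items + AN5 + AN7.
- Best: 11 × (4 − 0) + 4 + 4 = 52.
- Worst: 11 × (4 − 4) + 0 + 0 = 0.

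The rule gives 0 to 52, higher better, as stated. It is correct for 0–4 values.

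**Step 2: apply the same rule to the printed codes.** A patient with no fatigue on any item has code 1 throughout; one with most fatigue has code 5 throughout.
- Best: 11 × (4 − 1) + 1 + 1 = 35.
- Middle: 11 × (4 − 3) + 3 + 3 = 17.
- Worst: 11 × (4 − 5) + 5 + 5 = −1.
- Attainable extremes: 11 × (−1) + 1 + 1 = −9 and 11 × 3 + 5 + 5 = 43. These need contradictory answers (for example no fatigue on 11 items but no energy), so they are limits rather than typical values.

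**Step 3: what reaches the slope.** Let N be the correct contribution of the 11 items (0 to 44) and P that of AN5 and AN7 (0 to 8). The correct score is N + P. On printed codes each of the 11 items loses 1, and each of AN5 and AN7 becomes 5 minus its correct value:

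score as written = (N − 11) + (10 − P) = N − P − 1.

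The constant −1 cancels in a slope when items are complete; with missing items the proration rescales it, so cancellation is only approximate. The sign of P does not cancel. Moving AN5 and AN7 from *not at all* to *very much* lowers the score by 8 when it should raise it by 8.

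**Step 4: size.** A one-category improvement on every item should add 13 points. As written it adds 11 − 2 = 9, and 9/13 = 0.69. The factor depends on where the change lies: a difference confined to the 11 items is unchanged (factor 1), and one confined to AN5 and AN7 has its sign reversed (factor −1).

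**Step 5: possible repairs.** Subtracting 1 from every code gives best 11 × 4 + 0 + 0 = 44, middle 11 × 2 + 2 + 2 = 26, and worst 11 × 0 + 4 + 4 = 8. The attainable range is then 0 to 52 (11 × 0 + 0 + 0 to 11 × 4 + 4 + 4), so a range check would pass while AN5 and AN7 still counted backwards. Scoring all 13 items as 5 minus the printed code gives 13 × 4 = 52, 13 × 2 = 26 and 13 × 0 = 0.

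| Same category on all items | Correct | Rule on printed codes | Codes minus 1, then rule | 5 minus printed code |
|---|---|---|---|---|
| Best | 52 | 35 | 44 | 52 |
| Middle | 26 | 17 | 26 | 26 |
| Worst | 0 | −1 | 8 | 0 |

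**The case against.** The strongest reply is that Section 16.6.2.4 already defines item values by response label: zero is *not at all* and four is *very much*. On that reading the response to be subtracted from 4 is the 0–4 value, and the rule is complete and correct, as Step 1 shows. The form asks for a box to be marked under a verbal label, so the small printed numbers need not be what is stored. The coding in Rave is not shown, and a statistical analysis plan that was not available may settle it. Even if the wrong codes were used, item-level data would allow full recalculation.

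Much of this stands. A reader might infer that the endpoint will be mis-scored, or that scores generally leave the 0–52 scale. The protocol does not support either. Mis-scoring occurs only if the printed codes are what is stored and analysed. Even then, of the three uniform patterns only the worst (−1) lies outside 0 to 52; the other wrong scores look plausible.

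The reply does not remove the contradiction. The protocol fixes the rule, the range and the form, and the numbers on the form are not those the rule needs. Questionnaire booklets are printed for each patient (Section 6.11) and data are entered in Rave (Section 18.3), so entry of the numbers beside the boxes is a realistic route. The COST form in the same appendix is printed 0 to 4 and fits its own 4-minus rule, so the mismatch is particular to FACIT-Fatigue.

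**Conclusion.** The point holds as an internal inconsistency between Section 16.6.2.4 and Appendix II, not as an arithmetic error within the rule. Its effect is conditional. If values are stored by label as 0–4, there is none. If the printed codes are stored and scored as written, levels are wrong, and a between-arm difference in slope is attenuated to about 69% when it is spread evenly over the items, an assumption the data may not meet.

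A reader might also take this as a defect that must be fixed before the trial can be interpreted. It is a should-fix. FACIT-Fatigue is a secondary endpoint; the decision rules in Section 16.5.1.1 rest on acute toxicity and local control, and neither the sample size (Section 16.5.4) nor the stopping rules (Section 16.7.2) use the score.

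**What to change.** Add one sentence to Section 16.6.2.4: all 13 items are first recoded by response label, from *not at all* = 0 to *very much* = 4, whatever number is printed on the form, and the existing reversal, sum and proration then apply. Equivalently, replace the reversal step by 5 minus the printed code for all 13 items and keep the proration. Use one of the two, not both. Put the same rule in the Rave specification, check which values are stored for AN5 and AN7 in particular, and recode any data already entered. A simple test is that a form with no fatigue on any item must score 52 and one with most fatigue on every item must score 0; a check of the range alone is not enough. The cost is a sentence and a coding check, with no effect on patients, visits or sample size.

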### 2.2 Secondary Goals

The secondary objectives of the study are to evaluate:

- Patient Reported Quality of life [timeframe: 7 days after radiation treatment end date]
- Response rate [timeframe: at 3 months (+/- 14 days) post radiation treatment start date]
- Local control rate [timeframe: up to 24 months after the completion of radiation treatment]
- Relapse-free survival [timeframe: up to 24 months after completion of radiation treatment]

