7.2.5 Quality of Life

Patient Reported Outcomes will be collected at Baseline, End of Treatment, Day 7 post-RT, and 3 months post-RT completion date and will be based on the FACIT-Fatigue questionnaire within the windows defined in **Section 4.0**.

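### The only planned quality-of-life test is a post-treatment slope that omits baseline, does not estimate the Day 7 difference, and is zero or negative for 9 Gy when 9 Gy patients fare better

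*Protocol*

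**What the plan says.** Section 2.2 lists as the first secondary goal "Patient Reported Quality of life [timeframe: 7 days after radiation treatment end date". Section 16.3 describes the same endpoint as FACIT-Fatigue within 3 months after the end of radiation.

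The score is measured four times (Section 7.2.5): "Patient Reported Outcomes will be collected at Baseline, End of Treatment, Day 7 post-RT, and 3 months post-RT completion date". The test schedule in Section 4.0 agrees.

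The analysis is fixed in Section 16.6.2.4:

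- Target: "We will estimate the difference between treatment arms in the trajectory (slope) of the Fatigue Subscale score".
- Data: "including all available scores from end of treatment to 3 months post RT in a longitudinal mixed effects regression model with a random effect". Baseline is neither an outcome nor a covariate.
- Fixed effects: arm (9 Gy coded 1, 24 Gy coded 0), continuous time in weeks from end of treatment, and their interaction.
- Interpretation: "The estimates from the interaction term along with 95% confidence interval (profile likelihood) will be interpreted as the difference in trajectories between treatment arms".
- Test: "A likelihood ratio test will be used to compare treatment arms on the difference in trajectories of fatigue subscale score".
- Scale: "The Fatigue Subscale score ranges from 0 to 52 where a higher score indicates a better quality of life".

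No arm comparison at Day 7 or at any other visit is planned.

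**The concern.** The trial asks whether a lower dose spares patients acute harm. The fatigue pattern one would look for is a lower score at End of Treatment and Day 7 on 24 Gy, with recovery afterwards. The model's clock starts at End of Treatment, after any fatigue from radiation has arisen, and the only tested parameter is what happens from then on.

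A slope comparison carries no information on level. It is therefore uninformative about a steady benefit, and a benefit that fades makes it negative for the arm that did better early. At stake is the first-listed secondary goal: its one planned test does not address the stated question, and a level contrast chosen after seeing the data would be post hoc.

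**Working it through.** **Inputs from the protocol.** 51 evaluable patients per arm (Section 16.1). Post-treatment scores at End of Treatment (week 0), Day 7 (week 1) and 3 months (about week 13, window ±14 days; Section 4.0). Arm coding and scale direction from Section 16.6.2.4. The protocol gives no standard deviation, correlation, effect size or power for fatigue, so there is no stated figure to reproduce.

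**Step 1: what the interaction estimates.** With complete data and a random intercept, the interaction is the difference between arms in mean within-patient least-squares slope.

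- Mean time: (0 + 1 + 13)/3 = 4.667. Deviations: -4.667, -3.667, +8.333.
- Sum of squares: 21.78 + 13.44 + 69.44 = 104.67.
- Weights (deviation/104.67): End of Treatment -0.045, Day 7 -0.035, 3 months +0.080.

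The weights sum to zero. Day 7, the visit named in Section 2.2, enters with a negative weight: a better Day 7 score on 9 Gy lowers the estimate for 9 Gy.

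**Step 2: patterns of arm difference (9 Gy minus 24 Gy; higher is better).** The differences are illustrative assumptions.

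| Pattern | End of Treatment | Day 7 | 3 months | Interaction, points/week |
|---|---|---|---|---|
| Constant benefit | 4 | 4 | 4 | 0 |
| Early 24 Gy dip that recovers | 4 | 3.5 | 0 | -0.0446×4 - 0.0350×3.5 = -0.30 |
| Larger dip that recovers | 5 | 4.5 | 0 | -0.0446×5 - 0.0350×4.5 = -0.38 |

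The zero and the negative sign depend on no assumed variance. Moving the 3-month visit within its window changes only the size. At week 11 the weights are -4/74 and -3/74 for the first two visits, giving -(16 + 10.5)/74 = -0.36 for the 4, 3.5, 0 pattern. At week 15 they are -5.333/140.67 and -4.333/140.67, giving -(21.33 + 15.17)/140.67 = -0.26.

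**Step 3: how often the test would reject (assumed variances).** Simulation with 51 per arm, two-sided 0.05, total SD 8 to 12 and within-patient correlation 0.5 to 0.7, using a Wald test in place of the likelihood ratio test:

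- Constant 5-point benefit: the interaction rejects in 4.5% to 5.3% of runs, its false-positive rate. A baseline-adjusted Day 7 comparison rejects in 67% to 99%.
- Dip of 5, 4.5, 0 points: the interaction rejects in 64% to 99%, always with a negative sign. The baseline-adjusted Day 7 comparison estimates about +4.5 points for 9 Gy and rejects in 58% to 97%.

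**Step 4: what the unused baseline is worth at Day 7.** Assume between-patient SD 8 and residual SD 4, so total SD = √(64 + 16) = 8.94.

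- Unadjusted SE = 8.94 × √(2/51) = 1.77.
- Adjusted SE ≈ 1.77 × √(1 - r²): 1.53 at r = 0.5; 1.06 at r = 0.8 (1.07 in simulation).

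Those two SDs imply r = 64/80 = 0.8, the favourable end. For a 4-point Day 7 difference at two-sided 0.05, power is about 62% unadjusted, 74% at r = 0.5 and 96% at r = 0.8. At r = 0.5 with total SD 10 or 12 the adjusted power is 65% or 49%.

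**The case against.** The strongest reply has five parts.

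1. **The level difference is in the model.** This stands. With time zero at End of Treatment, the arm main effect is the End of Treatment difference. For means of 40, 40.5, 42 (9 Gy) and 36, 37, 42 (24 Gy), the planned mean model gives intercepts 40.17 and 36.27 and slopes 0.14 and 0.44. That is +3.90 at week 0 and 3.90 - 0.30 = +3.60 at Day 7, against a true 3.5. A reader might infer that the model cannot see a lasting benefit; that is too strong. What is blind to it is the only parameter the protocol tests and interprets.

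2. **The protocol never says the steeper slope wins.** This stands too. A reader might infer that the plan would declare fatigue better on 24 Gy, but Section 16.6.2.4 speaks only of a difference in trajectories. A negative interaction beside a positive main effect correctly describes convergence. The difficulty is that only the first of the two is to be tested or interpreted.

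3. **Day 7 may not be the target.** Section 16.3 gives 3 months, and the model's data range matches it. So the documents conflict on timeframe, and that needs settling. A 3-month horizon does not rescue a slope that ignores level.

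4. **Omitting baseline does no harm to the slope.** Correct: arms are randomised, so the slope contrast is not biased. Starting at End of Treatment also has a rationale, since Section 4.0 gives radiation as 5 against 16 days. The loss is precision for comparisons of level, and any estimate of change over radiation.

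5. **Model detail can wait for an analysis plan.** This holds for the covariance structure. If a random effect for patient means an intercept only, and patients recover at different speeds, the test may reject too often: about 6% to 12% at a nominal 5% for assumed patient-slope SDs of 0.2 to 0.6 per week, but 5.3% at 0.1. The wording does not exclude a random slope, so inflated type I error is not established. The choice of tested parameter, by contrast, is written into the protocol.

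**Conclusion.** The point holds in a limited form. The planned test does not estimate the Day 7 difference named in Section 2.2. Its expected value is zero under a constant benefit of any size, and negative for 9 Gy under an early 24 Gy dip that recovers (-0.30 points per week for differences of 4, 3.5 and 0). Both results follow from the visit times, the coding and the scale. The rejection rates and the precision gain do not: they rest on assumed SDs, correlations and effect sizes, and the gain from baseline ranges from modest (SE 1.77 to 1.53) to large (1.77 to about 1.06).

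A reader might infer that this endangers the trial's main conclusion. It does not: the decision rule in Section 16.5.1.1 uses acute toxicity and 2-year local control, not quality of life. The paragraph should be corrected, but the effect is limited to one secondary endpoint.

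**What to change.** First, reconcile the timeframe: Section 2.2 says Day 7, while Sections 16.3 and 16.6.2.4 run to 3 months.

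Then rewrite the analysis in Section 16.6.2.4:

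- Use a repeated-measures model with visit (End of Treatment, Day 7, 3 months) as a category, arm, arm-by-visit and the baseline score, with an unstructured covariance. Visits stay anchored to the end of radiation, so unequal treatment length is still handled.
- Name the baseline-adjusted arm difference at Day 7, with its 95% confidence interval and test, as the secondary estimate.
- Report the End of Treatment and 3-month differences from the same model alongside it.
- Keep the slope, if wanted, as a descriptive supplement.

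The cost is one rewritten paragraph and one aligned timeframe. All four assessments are already scheduled, so no visit, questionnaire or patient is added.
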